## Intervention Groups

The HTS intervention group will undergo HTS with conventional rehabilitation. The control group will undergo sham HTS with conventional rehabilitation.

### Blinding

The allocation sequence will be placed in sealed opaque envelopes kept in a location with restricted access. The envelopes will then be delivered to the researcher responsible for implementing the intervention the day prior to the beginning of the intervention. This process will be completed independently and the allocation sequence will be concealed from the therapists, outcome assessors, data analysts, participants, and participants’ relatives. The patients and their relatives will also be blinded to group allocation. Each participant will be identified with a particular number (rather than their name), which will be used by the outcome assessor. A blinded independent data analyst (who will not be involved in recruitment, eligibility screening, intervention delivery, or outcome assessment) will conduct the data analysis.

To ensure blinding, we will follow the sham stimulation schemes used in related studies the control group. For the sham stimulation, we will use sham coils, which are similar to real coils in terms of appearance, sound, and feeling (Ruohonen et al., 2000). The sham stimulation will be performed with the same HTS procedure (without stimulation) at the same location. The parameters on the equipment display will be identical in the HTS and sham groups.

## Intervention

### Supplementary Motor Area–Erb’s Point Conduction Time

The conduction time from the SMA to Erb’s point is defined as the latency between the motor evoked potential of the first dorsal interosseous muscles induced by SMA stimulation and the compound motor action potential evoked by Erb’s point stimulation. The conduction time will be used as the inter-stimulus interval in PAS.

### Patient Posture

The patients will be seated in a comfortable armchair, and will be asked to relax with their forearms placed on the armrest in a comfortable position. They will be awake during the whole intervention.

### Transcranial Magnetic Stimulation Parameters

TMS will be applied over the ipsilesional SMA using a figure-of-eight coil with 70-mm wing diameter and a Magstim Rapid 2 stimulator (Magstim Co., Ltd., Whitland, United Kingdom) with a stimulus intensity of 120% of the resting motor threshold (RMT). The RMT is defined as the lowest stimulus intensity (with ≥ 50 μV peak-to-valley amplitude) that is required to induce a motor evoked potential in at least 5 out of 10 stimulations. A neuronavigation system (Brainsight TMS, Rogue Research Inc., Montréal, Canada) will be used to precisely position the coil over the SMA sites, with the anatomical references being obtained from on individual T1-weighted magnetic resonance images. The SMA is located at the posterior part of the superior frontal gyrus and is bordered inferolaterally by the superior frontal sulcus and posteriorly by the precentral sulcus (Brodmann area 6).

### Peripheral Magnetic Stimulation Parameters

PMS will be applied over Erb’s point on the side with hemiparesis, with the forearms placed on a stable armrest in a neutral posture. The stimulation will be delivered by a 9-cm-diameter round-shaped coil. The patient’s neck will be flexed to the opposite side, about 20–30 degrees. The coil’s handle will be placed parallel to the brachial plexus. The intensity will be adjusted to induce a just-visible contraction of the abductor digiti minimi muscle (Evelyne et al., 2007).

### Hebbian-Type Stimulation/Paired Associative Stimulation Parameters

The PMS pulse will be delivered prior to the TMS pulse, with an inter-stimulus interval equal to the SMA–Erb’s point conduction time, which will be determined in advance (defined as the latency between the motor evoked potential of the first dorsal interosseous muscles induced by SMA stimulation and the compound motor action potential evoked by Erb’s point stimulation). Stimuli will be delivered at 0.2 Hz, with 100 pairs, lasting for approximately 8.3 min (Figure 1).

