Paired associative stimulation (PAS), based on Hebbian theory with a specific time interval, is an important means by which to reconstruct neural circuits. Traditionally, PAS was performed by delivering a peripheral afferent volley using electronic stimulation over the radial or median nerve prior to TMS over M1. Peripheral magnetic stimulation (PMS) can also be applied, for example to the muscles, spinal nerve roots, and peripheral nerve fibers. PMS can directly recruit 1A afferent fibers or indirectly provide strong proprioceptive inflow related to muscle contraction or the change in a joint angle, while peripheral electronic stimulation generates a significant cutaneous inflow in the afferent fibers of the lemniscus and spino-thalamic tract. Unlike peripheral electronic stimulation, PMS is painless and well tolerated (Beaulieu and Schneider, 2015). A study of 16 healthy participants revealed that PMS could modulate cortical excitability (Sato et al., 2016). Krewer et al. (2014) investigated the effect of repetitive PMS on upper-limb muscular spasm caused by stroke or brain trauma. They reported short-term effects on spasticity for wrist flexors and long-term effects on spasticity for elbow extensors (Krewer et al., 2014). Another group investigated the effect of integrated PMS and TMS in healthy participants. They found that PAS can upregulate corticospinal excitability and downregulate intracortical inhibition (Sato et al., 2016).

We aim to use PAS to rebuild a neural circuit involving SMA → internal capsule → periphery in order to restore motor function. We will perform timely coupled stimulation of presynaptic and postsynaptic neurons to restore the motor circuits instead of simply upregulating excitation in the lesion area. If HTS can be induced non-invasively by magnetically stimulating the peripheral nerve after magnetically stimulating the SMA in the human brain, this method may provide a neuromodulation approach to rebuild the motor network after stroke. We hypothesize that PMS of the peripheral nerve tens of milliseconds after TMS of the SMA related to the functioning of the upper extremities will induce spike timing-dependent plasticity. This will increase targeted cortical excitability and help to reconstruct sensorimotor pathway conduction to facilitate arm motor function recovery.

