This plasticity may depend on the functional overlapping regions in the sensorimotor network, which may compensate for the lost function after stroke. A study suggested a surrogate role for the SMA after M1 injury in monkeys. Before M1 injury, SMA neurons exhibited activity during learning (push-button task), which disappeared when performing the task after the task had been learnt. However, M1 injury led to SMA activity being restored when the task was performed again (Williams et al., 2006). This phenomenon is consistent with the ipsilesional SMA activation in stroke patients during rehabilitation (Hara, 2015). Zhang et al. (2016) found that compare to the health control functional connections between M1 and the ipsilesional parietal cortex, frontal gyrus, and SMA were increased in chronic stroke patients, while functional connections between bilateral M1 were decreased in stroke. Inman et al. (2012) found that the connections between the superior parietal cortex and M1, and the superior parietal cortex and the SMA, were significantly reduced in chronic stroke. The study of Jingchun et al. (2020) used fine map of fMRI showed that he CST originated from SMA are significantly related with motor outcomes in chronic stroke patients. The SMA/PMC is the key area for motor plan formation and movement initiation. The SMA/PMC and the prefrontal cortex form the brain’s cognitive network, which predicts the movements needed for tasks to be performed and receives information from the brain’s sensory integration network about the body’s spatial location, generating a primary task plan. Our study aims to restore the motor circuits, based on the ideas of Donald Hebb. He hypothesized that when the axon of cell A repeatedly or continuously participates in stimulating cell B, the synaptic connection between cell A and cell B will be strengthened. On this basis, Muming Poo found that long-term potentiation or depression can be produced by exciting the postsynaptic membrane 20 ms after or before exciting the presynaptic membrane, respectively, which is known as spike timing-dependent plasticity. The difference between spike timing-dependent plasticity and Hebbian theory is that the former emphasizes the role of the sequence of presynaptic and postsynaptic membrane excitation in synaptic remodeling (Zuzanna et al., 2019).

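### The intervention section gives the peripheral pulse before the cortical pulse, the reverse of the order in the trial's hypothesis

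*Protocol article*

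**What the plan says.** The article gives the pulse order in two sections.

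- **Intervention, Hebbian-Type Stimulation/Paired Associative Stimulation Parameters.** "The PMS pulse will be delivered prior to the TMS pulse", and the two are separated "with an inter-stimulus interval equal to the SMA–Erb’s point conduction time". The dose follows: "Stimuli will be delivered at 0.2 Hz, with 100 pairs, lasting for approximately 8.3 min". This is the only text that tells an operator which pulse comes first.
- **Background.** The aim is a descending pathway: "We aim to use PAS to rebuild a neural circuit involving SMA → internal capsule → periphery". The rationale speaks of "magnetically stimulating the peripheral nerve after magnetically stimulating the SMA in the human brain". The formal hypothesis has the same order: "We hypothesize that PMS of the peripheral nerve tens of milliseconds after TMS of the SMA". It names spike timing-dependent plasticity as the mechanism.

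The Discussion explains why order matters: "long-term potentiation or depression can be produced by exciting the postsynaptic membrane 20 ms after or before exciting the presynaptic membrane, respectively".

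**The concern.** The intervention section puts PMS first. The Background puts TMS of the SMA first, once in the rationale and once in the hypothesis. Both cannot describe the same treatment.

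In many trials a reversed word in a methods section would be minor. Here the treatment is defined by the relative timing of two pulses, and the theory invoked says that reversing them can reverse the effect. An operator who follows the intervention section as written delivers a different pairing from the one the trial says it tests.

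The first objective is whether the stimulation improves arm function, and the second is how it acts in the brain. With the order unresolved, a null result might mean that the idea fails or that the reverse pairing was given. A positive result would not support the descending-pathway explanation. No later analysis can separate these readings. If the order was changed or understood differently partway, the active arm would also mix two interventions.

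**Working it through.** **1. The statements side by side**

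| Section | First pulse | Second pulse |
|---|---|---|
| Background, rationale | TMS of the SMA | Peripheral |
| Background, hypothesis | TMS of the SMA | PMS, tens of milliseconds later |
| Stimulation parameters | PMS | TMS, after the conduction time |

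**2. Does anything else settle it?** The section on SMA–Erb's point conduction time defines how the interval is measured, not which pulse leads. The caption of Figure 1 refers only to joint central and peripheral stimulation. The drawing itself was not available for this review. It may show an order, but even so the two sections of text would still conflict.

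**3. What the order means under the article's own theory.** The target pathway runs from the SMA to the periphery, so the SMA is the presynaptic side. By the Discussion's account, exciting the postsynaptic side after the presynaptic side gives potentiation, and exciting it before gives depression. If PMS stands for the postsynaptic excitation, the Background order is the potentiating one and the intervention section's order is the depressing one.

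**4. Timing at Erb's point.** Set TMS at time 0 and let c be the conduction time, which is also the interval between pulses. The descending volley reaches Erb's point at +c.

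- TMS first: PMS falls at +c. Offset = c − c = 0.
- PMS first: PMS falls at −c. Offset = c − (−c) = 2c.

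The article gives no value for c, which is measured in each participant, so the offset stays in units of c.

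**5. Exposure.** The stated session length reproduces: 100 pairs ÷ 0.2 Hz = 500 s, and 500 ÷ 60 = 8.3 min. Over the full course, 100 pairs × 25 sessions = 2,500 pairs for each participant who completes active treatment, in an arm planned at 45. This counts how many pairs the order governs. It does not measure the effect on outcome.

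**6. What does not change.** The sample size, significance level and analysis do not depend on pulse order.

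**The case against.** The strongest reply is that the intervention section may contain a slip of one phrase. The Background describes the conventional method in the peripheral-first order: "Traditionally, PAS was performed by delivering a peripheral afferent volley using electronic stimulation over the radial or median nerve prior to TMS over M1". That wording could have been carried into the intervention section while the device was set up correctly. This is plausible, and the article cannot exclude it. It limits what can be said about the delivered order, but the operative instruction is still wrong under the stated hypothesis.

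A second reply is that peripheral-first pairing may itself be sound. The Background says that PMS can recruit afferent fibres and that combined PMS and TMS raised corticospinal excitability in healthy people, without stating the order used. The Discussion's rule concerns two sides of a single synapse, and the article never says that a pulse at Erb's point is the postsynaptic event. This stands: depression, and hence harm, is a possibility drawn from the article's theory and is not shown. For the same reason, the 2c offset describes timing at the nerve and does not measure clinical consequence. Even so, peripheral-first is an ascending pairing, and the Background sets out a descending one.

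A third reply is that the first objective names no pulse order, so the comparison with sham answers it for whatever was delivered. That is right if delivery was consistent. What is lost is the link to the hypothesis, the mechanistic reading and the ability to replicate the treatment.

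**Conclusion.** The concern holds. The intervention section and the hypothesis give opposite pulse orders, and no text reconciles them. As written, the trial may deliver the reverse of the pairing it sets out to test.

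The contradiction itself is certain from the text. Its size is a shift of 2c in the peripheral pulse relative to TMS, with the sign reversed, for up to 2,500 pairs per completing active participant. That figure assumes the intervention section is followed as written. The reading of one order as potentiating and the other as depressing further assumes that the SMA is the presynaptic side and PMS the postsynaptic event, as the Background's stated circuit and mechanism imply.

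The point should be settled before more participants are treated. The article gives a recruitment start of 11 November 2020 in one section and 1 December 2020 in another. Both precede the protocol version dated 21 February 2021, so some participants may already have been treated.

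**What to change.** 1. State one order, in the same words, in the Background hypothesis, the intervention section, Figure 1 and any set-up instructions used at the device. If the hypothesis stands, the instruction should read: TMS over the SMA first, then PMS at Erb's point after the individually measured conduction time. If peripheral-first is intended, rewrite the hypothesis, rationale and Discussion for an ascending pairing.
2. Confirm which order treated participants received, from stimulator logs or session records. The article does not mention such records, so their existence is an assumption. If none exist, ask the operators and document the answer.
3. From now on, record pulse order and interval at every session.
4. If some participants received the other order, keep them in the planned comparison of active with sham treatment and report results by order as an addition. They should not be dropped on this ground.

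The cost is a protocol clarification or amendment, a check of records and one more line on the session form. No extra patients or procedures are needed.

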**FIGURE 1 F1:**
[figure not shown]
Hebbian-type stimulation (HTS). This figure is a schema chart of the intervention model of the study. In the figure, the purple area on the head is the primary sensory area, the red area is the primary motor cortex, and the position of the coil is the SMA area. In this study, the joint stimulation of the central and peripheral was used to reconstruct the pathway from the SMA area to the peripheral nerve.

### Intervention Stimulation

The intervention will be conducted once a day, 5 days per week, for 25 sessions in total.

### Sham Stimulation

For the sham stimulation, we will place the sham coils in the same position as in SMA TCM and PMS. The strength and frequency of the sham coil clicking noise will be similar to the real clicking noise (but with no magnetic stimulation).

### Basic Stroke Management

Each participant in both groups will receive basic stroke management, including (1) assessments at the level of body function/structure, activities and participation and environmental Factors described in the International Classification of Functioning, Disability, and Health (ICF) (Svestková, 2008), (2) rehabilitation services (delivered by a multidisciplinary team of neurologists, rehabilitation physicians, rehabilitation nurses, occupational therapists, physical therapists, and speech and language therapists) based on the recommendations of clinical guidelines for patients with stroke (Winstein et al., 2016), and (3) medications(e.g., antihypertensive drugs, anti-platelet medicine, hypoglycemia agents, anti-spasm drugs etc.).

## Assessments

The clinical assessments will be performed at baseline (on the day of enrollment), immediately after the 5-week HTS/sham intervention, and at the 3-month follow-up after the intervention. After recruitment and eligibility screening, the following data will be collected: sociodemographic data (date of birth, gender, laterality, marital status, and occupational status), neuroimaging results, disease and current episode duration, blood pressure, comorbidities (psychiatric, addiction, and somatic diseases), medications, and degree of prior resistance to other treatments. These variables will be evaluated at baseline, immediately after the 5-week HTS/sham intervention, and at the 3-month follow-up (along with WMFT, FMA-UE, FIM, and fNIRS) (Table 1).

**TABLE 1 T1:** Study timeline.

	Enrolment	Baseline assessment	Intervention phase		Post-treatment assessment	Follow-up assessment
Time point	−T_1w_	T_0_	T_0_	T_5w_	T_5w_	T_3months_
Enrolment						
Eligibility screening	×					
Informed consent	×					
Allocation	×					
Interventions						
Hebbian-type stimulation (HTS)						
Sham stimulation						
Primary outcome						
Wolf Motor Function Test (WMFT)		×			×	×
Secondary outcomes						
Fugl-Meyer Assessment (FMA)		×			×	×
Functional Independence Measure (FAM)		×			×	×
Functional near-infrared spectroscopy (fNIRS) parameters		×			×	

## Adverse Events and Safety Considerations

Data on all potential AEs will be obtained from the participants and recorded in an observation table by the researchers (including time and date of occurrence, severity, treatment parameters, and potential causal relationship with the intervention). Monitoring of AEs will be carried out by the treating physical therapists. The principal researcher ([name]) and data security management members will immediately be informed about severe AEs. AEs might include transient upper limb weakness, muscle soreness in the stimulation area, headache, increased muscle tone in the upper extremities, and hearing loss (caused by the coil noise during stimulation). We will give the patients earplugs to prevent hearing impairment during stimulation, and when the treatment is over, we will conduct a hearing assessment for all patients who report aural fullness, hearing loss, or tinnitus. The most serious acute AEs of TMS is epileptic seizure. Patients will be carefully asked if they have a disease that may cause epilepsy or are taking drugs that may increase the risk of epilepsy or reduce cortical excitability, and those who do will be excluded prior to randomization. If epileptic seizure occurs, the stimulation will be stopped and acute treatment will immediately be provided (Rossi et al., 2021).

## Maximizing Treatment Compliance and Minimizing Dropout Rate

To strengthen treatment compliance and minimize dropout, a doctor will contact the participants regularly by phone to confirm the appointments, assess the effect of the treatment, and discuss the subsequent treatment and any issues that may interfere with compliance.

### Primary Outcomes

WMFT is highly recommended to assess the motor ability of patients with moderate to severe upper extremity motor deficits in research and clinical settings (Wolf et al., 1989). Its test-retest and inter-rater reliability and internal consistency range from 0.88 to 0.98, with most of the values being close to 0.95 (Morris et al., 2001). It will be used to assess upper limb movement ability, encompassing 17 upper-extremity motor tasks that involve starting position and verbal instructions (Wolf et al., 2001). The Functional Ability Scale score for each task ranges from 0 to 5. It is an effective and sensitive method to assess the upper extremity functional ability of patients with moderate to severe impairments after stroke (Hodics et al., 2012).

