## Trial Design

This protocol has been designed according to the Standard Protocol Items: Recommendations for Interventional Trials (SPIRIT) guidelines. It is registered with the Chinese Clinical Trial Registry. Based on a 1:1 ratio, 90 participants will be randomly assigned to the HTS and sham groups. The prospective, single-center, double-blind, randomized, sham-controlled clinical trial will study the therapeutic effects of HTS vs. sham intervention. Each patient will undergo 1 session of real/sham HTS per day, always followed by general rehabilitation therapy, 5 days per week, with a total of 25 sessions. Three assessments will be performed in both groups: at baseline, immediately after the 5-week treatment, and at a 3-month follow-up. The effects will be measured using a variety of rating scales. The primary outcome will be the Wolf Motor Function Test (WMFT). The secondary outcomes will be the Fugl-Meyer Assessment for Upper Extremity (FMA-UE), Functional Independence Measure (FIM), and fNIRS parameters. To strengthen treatment compliance and minimize dropout, a doctor will contact the participants regularly.

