## Eligibility Criteria

The inclusion criteria are as follows:

(1) Having a first unilateral supratentorial, ischemic stroke, and having had a stroke in 4–12 month;

(2) Upper extremity dysfunction, with FMA-UE motor score of 30–60 out of 66 (Fugl-Meyer et al., 1975);

(3) Aged 18–80 years, regardless of sex;

(4) Mini Mental State Examination (MMSE) score > 24;

(5) Written informed consent;

(6) Right handedness.

The exclusion criteria (based on the TMS safety criteria proposed by Wassermann, 1998) are as follows:

(1) Metal implant device in the head, neck, or stimulation area;

(2) Medical implant device (cardiac pacemaker or cochlea implant);

(3) Pregnancy;

(4) Current or history of epilepsy;

(5) Current or history of medications known to affect central nervous system excitability;

(6) Intracranial hypertension;

(7) Unstable fractures or joint contracture.

(8) Taking drugs that may increase the risk of epilepsy or reduce cortical excitability.

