## Sample Size Estimation

The calculation of the sample size was based on data from previous research and our per experiment (Lai et al., 2015). As the study involves two groups, the following sample size calculation for a two-sample mean comparison was used:

$$n_{c}=\frac{{\left(Z_{1-\alpha }+Z_{1-\beta }\right)}^{2}\,\sigma^{2}\,\left(1+\frac{1}{K}\right)}{{\left(\mu_{T}-\mu_{C}-△\right)}^{2}}$$

where, Z_1–_*_α_* = 1.960, Z_1–_*_β_* = 0.842, μ_*T*_=6.6 (predicted mean in HTS group); μ_*C*_=2.3 (predicted mean in sham group), σ = 2.0 (standard deviation), *K* = 1 (ratio of participants in the HTS and sham groups), Δ = 3 (optimality bounds), α = 0.025 (2.5% one-tailed significance level), and β = 0.20 (80% power). The calculated required sample size was 37 participants per group. Assuming a 20% dropout rate, 45 participants per group (a total of 90 participants) need to be recruited.

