### Statistical Analysis

Statistical analysis will be performed using SPSS 22.0 (SPSS Inc., Chicago, IL, United States). Database management and statistical analysis will be performed by an independent researcher, who will be blinded to group allocation. Monitoring of AEs will be carried out by the treating physical therapists. The primary analysis, which will be a per-protocol analysis, will include the patients who underwent the treatment course and completed the 3-month follow-up.

Descriptive statistics will be used to describe the baseline characteristics of the participants in both groups. The normally distributed continuous data will be presented as mean ± standard deviation, and the non-normally distributed continuous data will be presented as median (maximum and minimum). The Shapiro–Wilk test will be used to evaluate data normality. Homogeneity of variance will be assessed by Levene’s test. For the normally distributed continuous data (including WMFT, UE-FMA, and FIM), paired *t*-tests will be used to compare between baseline and postintervention in each group. Additionally, unpaired *t*-tests will be used to assess the differences in the baseline characteristics and the primary and secondary outcomes between the HTS and sham groups. For the non-normally distributed continuous data, Wilcoxon tests will be used. The one-tailed significance level (α) for statistical hypothesis testing will be set at *P* < 0.025 (Figure 2).

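### The planning figures (6.6 vs 2.3, SD 2.0, margin 3) are tied to no stated WMFT quantity, and the between-group test is not written on the one Functional Ability reading that fits them

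*Protocol article*

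**What the plan says.** All references are to the Protocol article.

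- **Trial Design** names the primary outcome as the WMFT and adds no summary measure.
- **Primary Outcomes** describes it as "encompassing 17 upper-extremity motor tasks that involve starting position and verbal instructions" and adds: "The Functional Ability Scale score for each task ranges from 0 to 5". It does not say whether the endpoint is the sum, the mean or a performance time, or whether it is a level or a change.
- **Sample Size Estimation** uses 6.6, labelled "predicted mean in HTS group", and 2.3, labelled "predicted mean in sham group", with a standard deviation of 2.0 and Δ = 3. The section attributes its data to previous research and the group's own preliminary experiment. It names no outcome, unit or visit.
- **Eligibility Criteria** admits patients with "Upper extremity dysfunction, with FMA-UE motor score of 30–60 out of 66".
- **Statistical Analysis** states that "unpaired *t*-tests will be used to assess the differences in the baseline characteristics and the primary and secondary outcomes between the HTS and sham groups". Baseline and post-intervention values are set against each other only in the separate paired tests within each group.

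**The concern.** A sample size holds only for the variable whose mean and SD went into it. Here the article prints the planning figures, the scoring range and the test, so the three can be compared, and they do not line up. The test as worded takes the outcome score itself. The planning means look like gains.

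This matters because the spread of raw scores between patients is usually much larger than the spread of within-patient changes. An analyst who follows the text would compare post-treatment WMFT scores across patients admitted over a 30-point range of FMA-UE. That comparison could have far less power than the one planned, although baseline WMFT is collected and could be used.

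**Working it through.** **1. Reproduce the stated size.** The inputs are those of Sample Size Estimation: 1.960, 0.842, σ = 2.0, K = 1, and an effective difference of 6.6 − 2.3 − 3 = 1.3.

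n = 2 × 2.0² × (1.960 + 0.842)² / 1.3² = 37.17 per group, against 37 stated. Power at 37 per group is Φ(1.3 / (2.0 × √(2/37)) − 1.96) = 79.8%. The arithmetic is as described; what is open is the variable.

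**2. Compare the figures with each Functional Ability reading.** The 17-task total runs from 0 to 17 × 5 = 85.

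| Reading | Check | Result |
|---|---|---|
| Mean item score, level | 6.6 > maximum of 5 | impossible |
| Mean item score, change | largest possible gain is 5 | impossible |
| Total, post-treatment level | 6.6/85 = 7.8% and 2.3/85 = 2.7% of range; 6.6/17 = 0.39 and 2.3/17 = 0.14 points per task | arithmetically possible, not credible |
| Total, change from baseline | average gains of 0.39 vs 0.14 points per task | fits the means |

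The third row is not credible because entry requires 30/66 = 45% to 60/66 = 91% of the FMA-UE maximum. An arm in that range would not be expected to score about 3% to 8% of the WMFT total.

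**3. Power if raw post-treatment totals are compared as written.** Under randomisation the expected baseline difference is zero, so a 4.3-point difference in mean change is also a 4.3-point difference in post-treatment means. Only the SD changes. The document gives no SD for WMFT totals, so a range is assumed. Its upper value takes baseline FMA-UE as uniform on 30–60, SD 30/√12 = 8.66, and rescales it in proportion to 85 points: 8.66 × 85/66 = 11.15.

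Power = Φ(d / (SD × √(2/37)) − 1.96), with d = 4.3 against zero, or d = 4.3 − 3 = 1.3 against the margin.

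| Assumed SD of raw total | Against zero | Against margin of 3 |
|---|---|---|
| 8 | 64% | 10% |
| 10 | 46% | 8% |
| 11.15 | 38% | 7% |

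Both columns are shown because the margin is in the sample size formula, while the t-test is described without one.

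**4. Power if change in the total is compared.** At the planned SD of 2.0, power against the margin is 79.8%, as in step 1. Against zero, with d = 4.3, power stays above 99% at an SD of 3.5 and is 92% at 5.5.

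**The case against.** *A reading does fit.* A reader might infer that the figures match no possible WMFT score. The document does not support that. A change in the 0–85 total fits 6.6 against 2.3. A performance-time reading cannot be excluded either, because no time metric is given to test against. What stands is that no stated quantity is attached to the figures.

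*The SD of 2.0 may be sound for change.* A reader might also infer from the quoted reliability, mostly near 0.95, that 2.0 is too small even for change scores. That cannot be shown. The inference needs a between-patient SD that the document does not give. The quoted range of 0.88 to 0.98 also pools test-retest, inter-rater and internal-consistency figures. With change SD = s × √(2(1 − r)) and r = 0.95, 2.0 corresponds to s = 6.3; with r = 0.98, to s = 10. The SD needs confirming, but it is not refuted.

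*A null result need not be uninterpretable.* Step 4 shows that on the change reading, tested against zero, power is high even at SDs well above 2.0. This stands, and it confines the power loss against zero to the comparison of raw scores.

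*This is a condensed article.* Scoring details may be left to a fuller document. That excuses silence on sum or mean. It does not excuse printed planning figures that cannot belong to some readings of the printed scale, next to a printed test on the outcome itself.

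**Conclusion.** The point holds as a mismatch between planning figures and written test. Two of the four Functional Ability readings are impossible and a third is not credible. The one that fits, change in the 17-task total, is not what the between-group test says. These statements need only the document's own numbers and the entry criterion.

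The size of the power loss rests on assumptions: the SDs of 8 to 11.15 for raw totals, and a true difference of 4.3 points. Across that range, power against zero falls to 64–38%, and against the margin to 10–7%, compared with the stated 80%.

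It does not follow that the trial is underpowered under every analysis, or that the figures describe some other variable. Their source is not visible, so the correspondence is unstated and the written test does not secure it. The correction is cheap and should be made before the data are analysed.

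**What to change.** 1. Check against the pre-experiment data which WMFT quantity (sum, mean or time; level or change) and which visit 6.6, 2.3, 2.0 and 3 refer to. State this in Sample Size Estimation. The origin of the figures should be verified, not presumed.
2. If they are changes in the 0–85 total, define the primary endpoint in Primary Outcomes and Statistical Analysis as change from baseline in that total. Name one visit, either the end of the 5-week treatment or the 3-month follow-up, and run the between-group test on that quantity.
3. Confirm the SD on that scale. If it is above 2.0, restate the power at 37 per group.

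The cost is wording and one recalculation. Baseline and both later WMFT assessments are already scheduled, so these steps add no procedures. The stated power may become less favourable.
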